### Randomization of participants

3.5

The subjects were randomly assigned to one of the two treatment groups, using a simple randomization scheme generated by a software (www.randomization.com). Individual, sequentially numbered index cards with the random assignments were prepared. The index cards were folded, and placed in sealed opaque envelopes

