### Eligibility criteria

3.2

We will enroll 40 MS patients affected by gait disturbances and moderate-severe spasticity: 20 of them in treatment with Sativex (Group A) considered as responders, and 20 treated only with the most common antispastics used in MS (Group B). Inclusion criteria are: age range 18 to 65 years; diagnosis of definite relapsing-remitting or primary-progressive or secondary-progressive multiple sclerosis; absence of clinical relapses from no gadolinium-enhanced lesions on brain and spinal cord MRI performed at least 6 months before study entry; no mood or sleep disorders with an Hamilton score of ≤17; a moderate to severe spasticity in at least 2 districts of upper and/or lower limbs; absence of clinical or neuroradiological relapses from at least 6 months before study entry; Expanded Disability Status Scale (EDSS) total score between 3.5 and 7.0; no history of psychosis; no presence of pace-maker, aneurysms clips, neurostimulator or brain/subdural electrodes (safety TMS procedure); right handedness, central conduction time in upper limbs of <8 ms; no robotic gait training contraindications.

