### Prescreening

3.4

We evaluated 90 MS patients attending the tertiary MS Center of the IRCCS “Bonino-Pulejo” with a moderate to severe spasticity despite oral antispastic treatment (i.e., Baclofen) and a gait disturbance. We randomly divided the population in 2 groups: one with the same oral therapy and the second with Sativex in add-on. After 1 month, we evaluated the response to Sativex (responder patients’ amelioration >20% at MRS score). We included into the study the first 20 patient responders to Sativex and 20 who continued their ongoing antispastic treatment.

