### Study population

3.6

All the 40 subjects, divided into 2 groups (A: Sativex + Lokomat Training, and B: other antispastics + Lokomat training) will perform a RAGT (each session will last at least 45 minutes, 3 times per week, for a total of 20 sessions).

All the patients will undergo a complete physical and neurological examination, including the evaluation of disability by means of the EDSS, the assessment of spasticity using the Modified Ashworth Scale (MAS), and the numerical rating scale (NRS). To clarify the role of Sativex in improving spasticity gait-related symptoms, we will also administer the following scales: 10 meters walking test (10WT) and Ambulation Index (AI). Quality of life will be evaluated by means of MS quality of life 54 (MSQOL-54). The skilled clinician will be blind to the drug treatment. Moreover, we will evaluate some electrophysiological parameters to test cortical excitability: motor-evoked potentials (MEP) amplitude, short intracortical inhibition (SICI) and facilitation (ICF) from the abductor pollicis brevis muscle (APB) of the most affected side. The same assessment will be applied at baseline, at the end of the RAGT (T1), and 30 days after the end of the neurorehabilitation training (T2).

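### Simple, unstratified allocation and models without a baseline prognostic factor leave a possible chance imbalance in EDSS or MS course uncorrected at 20 per group

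*Protocol article*

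**What the plan says.** - **Allocation.** The section Randomization of participants says: "The subjects were randomly assigned to one of the two treatment groups, using a simple randomization scheme generated by a software". The assignments are on numbered cards in sealed opaque envelopes. No block or stratification factor is named.
- **Population.** Eligibility criteria admits a "diagnosis of definite relapsing-remitting or primary-progressive or secondary-progressive multiple sclerosis" and an "Expanded Disability Status Scale (EDSS) total score between 3.5 and 7.0". The same section fixes 20 patients in each group.
- **How the groups arise.** Prescreening says: "We evaluated 90 MS patients attending the tertiary MS Center". It continues: "We randomly divided the population in 2 groups: one with the same oral therapy and the second with Sativex in add-on". After one month, it says: "We included into the study the first 20 patient responders to Sativex and 20 who continued their ongoing antispastic treatment".
- **Outcomes.** Study population lists the 10-metre walk and the Ambulation Index, with EDSS assessed at baseline, T1 and T2. Outcome measures adds the 6-minute walk.
- **Analysis.** Statistical analysis gives signed-rank tests on the changes between visits for the clinical and walking outcomes, carried out in both groups. It gives a repeated-measures ANOVA with time and group for motor threshold, MEP amplitude, SICI and ICF. Neither EDSS nor MS course appears as a factor or covariate. The section also calls the trial a pilot whose 40 patients were chosen for feasibility.

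**The concern.** Simple randomisation balances patient characteristics only on average. With 20 per group, one realised comparison can be noticeably uneven. EDSS and disease course are plausible predictors of walking and of how much walking changes with training, and both are known at entry. The document gives no figure for the strength of that relation.

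An uneven mix can be handled at allocation, by stratifying, or at analysis, by adjusting. The article states neither. If more disabled patients gain more or less from robotic training, an uneven EDSS mix would shift the difference in change between A and B. The trial is meant to inform a confirmatory study, so such a shift would carry over into its planning.

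**Working it through.** The plan gives no figure on imbalance, so there is none to reproduce. The calculations below treat the two analysed groups as random samples of 20. The last step asks what happens when that does not hold.

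**Inputs from the article:** 20 per group; EDSS 3.5 to 7.0; three MS courses; 90 patients randomised before the one-month response test.

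**Assumed, because the article gives no figure:** share of patients with a given factor, 0.2 to 0.6; EDSS standard deviation, 0.8 to 1.15 (1.15 is a uniform spread over the half-point steps from 3.5 to 7.0).

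**1. A yes/no factor present in half of patients** (for example EDSS above the median). Let X and Y be independent Bin(20, 0.5) counts in A and B. Then X + (20 − Y) follows Bin(40, 0.5), so:
- At least 20 points apart (4 patients of 20): P(|X − Y| ≥ 4) = 2 × P(Bin(40, 0.5) ≤ 16) = 0.268.
- At least 30 points apart (6 patients of 20): P(|X − Y| ≥ 6) = 2 × P(Bin(40, 0.5) ≤ 14) = 0.081.

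For one MS course with another share p, the exact difference of two Bin(20, p) counts gives:
- p = 0.2: 16% for at least 20 points, 3% for at least 30 points.
- p = 0.33: 24% and 6%.
- p = 0.6: 26% and 7.5%.

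**2. A continuous factor.** The standardised difference d between group means is approximately N(0, 2/20), so its standard error is √0.1 = 0.316 SD and P(|d| > t) = 2 × (1 − Φ(t/0.316)).
- t = 0.2: 53%
- t = 0.3: 34%
- t = 0.5: 11%
- t = 0.8: 1%

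In EDSS units, mean scores differ by more than 0.5 point with probability 5% (SD 0.8), 11% (SD 1.0) or 17% (SD 1.15).

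**3. Effect on the comparison.** Shift in the group difference = imbalance × difference in outcome between the factor's levels. If the factor moves an outcome by 0.5 to 1.0 SD (assumption):
- A 20-point imbalance moves the group difference by 0.2 × 0.5 = 0.10 to 0.2 × 1.0 = 0.20 SD.
- A 30-point imbalance moves it by 0.3 × 0.5 = 0.15 to 0.3 × 1.0 = 0.30 SD.

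These shifts apply to outcomes compared as levels. When change is compared, only the difference in *change* between EDSS levels counts, because stable differences in level cancel. The document gives no value for it.

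**4. What selection on response adds.** Simulation of 45 v 45 (arm sizes assumed), keeping the first 20 responders in the Sativex arm and 20 unselected controls. Assumed response is 45% to 75%.
- Correlation 0 between baseline walking and response: P(|d| > 0.5 SD) stays at 11% to 12%, as in step 2.
- Correlation 0.3 to 0.5: expected imbalance is 0.12 to 0.44 SD, and P(|d| > 0.5 SD) is 14% to 42%.

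This second imbalance is systematic. Stratifying the 90 at randomisation would not remove it, because the 20 responders are picked afterwards and in one arm only.

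**The case against.** The case against is substantial, and much of it stands.

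- **Simple randomisation is valid.** Chance imbalance is already covered by the error rate of the test, and a feasibility pilot may do without strata. This stands, so the point is about a better choice and not an error.
- **Each patient serves as his or her own control.** The walking outcomes are analysed as within-patient changes, so stable differences due to EDSS or course drop out. This stands. What remains is that change itself may differ by EDSS.
- **Covariates are commonly left to an analysis plan.** This is fair: if an unseen plan already adjusts for EDSS, the analysis part of the point is met. However, the article does write out the factors of its ANOVA, and these are time and group only.
- **Allocation may be over.** Prescreening and Randomization of participants are written in the past tense, so a new list may come too late. The adjusted analysis remains available.
- **The analysed groups are not the groups as randomised.** This is correct, and it limits steps 1 and 2 to the case of random samples.

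Two stronger readings should be resisted. From the phrase "All the 40 subjects, divided into 2 groups", a reader might infer that 40 patients were put on a simple list that could hardly yield equal groups. Prescreening instead describes randomising 90 and then filling each group to 20, so the equal split does not come from the list. A reader might also scale the possible shift against the effect size of 0.61 in Sample size. That figure is given for an interaction, without a metric, so the comparison has no firm meaning.

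**Conclusion.** The point holds as a modest one. Allocation is simple and unstratified, the stated analyses use no baseline prognostic factor, and 20 per group leaves room for chance imbalance: about 27% for at least 20 percentage points and about 8% for at least 30, for a factor present in half of patients. These figures assume that both groups are random samples. The effect on the estimated difference in change cannot be fixed from the document.

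A reader might infer that a sizeable imbalance is likely. The figures do not support that: beyond 0.3 SD it is 34% and beyond 0.5 SD it is 11%. Only a small imbalance, beyond 0.2 SD, is more likely than not (53%). Nor would stratification make the groups comparable. Group A is selected on response after randomisation, and that systematic problem is larger and has to be dealt with separately.

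**What to change.** **Analysis (possible even if allocation is complete).** State a between-group comparison of A and B on change in the walking and neurophysiological outcomes, adjusted for baseline EDSS and for the baseline value of the outcome, so that change differing by EDSS is accounted for. EDSS is required for eligibility and is already assessed at baseline under Study population, so no new data are needed. The cost is one or two sentences and two degrees of freedom per comparison: with 40 patients, 40 − 4 = 36 residual degrees of freedom instead of 40 − 2 = 38.

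**Allocation (only for patients not yet allocated).** Replace the simple list with computer-generated permuted blocks of varying, concealed size, stratified by two EDSS bands, and keep the sealed numbered envelopes. The cost is a new list and one protocol sentence. The downside is slightly greater predictability in a single centre where the drug is open. Varying block sizes limit this.

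**Statement of limits.** Say in the text that neither step removes the imbalance from selecting Sativex responders after randomisation. Adjustment can account only for the part that runs through the measured covariates.

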### Study population

3.6

All the 40 subjects, divided into 2 groups (A: Sativex + Lokomat Training, and B: other antispastics + Lokomat training) will perform a RAGT (each session will last at least 45 minutes, 3 times per week, for a total of 20 sessions).

All the patients will undergo a complete physical and neurological examination, including the evaluation of disability by means of the EDSS, the assessment of spasticity using the Modified Ashworth Scale (MAS), and the numerical rating scale (NRS). To clarify the role of Sativex in improving spasticity gait-related symptoms, we will also administer the following scales: 10 meters walking test (10WT) and Ambulation Index (AI). Quality of life will be evaluated by means of MS quality of life 54 (MSQOL-54). The skilled clinician will be blind to the drug treatment. Moreover, we will evaluate some electrophysiological parameters to test cortical excitability: motor-evoked potentials (MEP) amplitude, short intracortical inhibition (SICI) and facilitation (ICF) from the abductor pollicis brevis muscle (APB) of the most affected side. The same assessment will be applied at baseline, at the end of the RAGT (T1), and 30 days after the end of the neurorehabilitation training (T2).

### Study drug

3.7

Patients in treatment with Sativex will receive cannabis-based medicine extract presented in a pump action sublingual spray. Sativex is composed of whole cannabis plant extract, containing THC (27 mg/mL) and CBD (25 mg/mL), in ethanol/propylene glycol (50:50) excipient. Each actuation delivers 100 KL of spray, containing THC 2.7 mg and CBD 2.5 mg.

Sativex is indicated as treatment for symptom improvement in adult patients with moderate to severe spasticity due to MS, who have not responded adequately to other antispasticity medication and who demonstrate clinically significant improvement in spasticity-related symptoms during an initial trial of therapy (4 weeks). The drug is intended to be taken with another antispastic medication, and treatment should be started under the supervision of a doctor skilled in MS. The number and frequency of dosing (sprays) with Sativex will vary and the correct dose of Sativex for the individual patient might be reached over a couple of weeks. The most common side effects or adverse effects associated with the first 4 weeks of treatment with Sativex in clinical studies of the drug were dizziness (occurring mostly during the early stages of treatment when the dose is titrated) and fatigue. During the initial Sativex titration period, it is necessary to gradually increase the number of sprays that you take per day. You should leave at least 15 minutes between sprays and should not exceed 12 sprays per day.

### Neurorobotic treatment

3.8

The neurorobotic treatment will be performed by using the Lokomat (Lokomat, Hocoma, Volketswil, Switzerland) device. The Lokomat is a robotic device, consisting of a powered gait orthosis with integrated computer-controlled linear actuators at each hip and knee joint, a BWS, and a treadmill. Gait pattern and guidance force are individually adjustable to the patient's needs to optimize the functional training in the sagittal, frontal, and transverse planes. Moreover, the new Free-D module allows pelvic rotation and weight shifting with a more physiological deambulation. The system can also evaluate the physiologic stiffness of the patient's hip and knee joints and the isometric force exerted, respectively, for hip and knee extension by the L-STIFF and the L-FORCE software module. The workload will be progressively adjusted based on the improvement of motor performances. Training parameters (weight support, gait speed, guide force) will be individually adapted. During the first Lokomat session, support will be set at 50% of the body weight and will be adapted on observation of the gait. In particular, after 2 weeks, the body weight support will be probably reduced to 30% and in another 2 weeks to 20% of the patient's body weight.

The Lokomat motor guidance system will be first set at 100%, corresponding to a passive walk. The guidance will be reduced as much as possible on observation of the gait pattern. Walking speed will be regulated on observation of gait and will change randomly to simulate normal gait. The locomotor treatment will be administered 3 times per week for 4 weeks. The overall duration of Lokomat therapy, including the time getting in and out, is expected to be 45 minutes, whereas the effective robotic gait training will last about 30 minutes. At the beginning of the treatment, 40% of each patient's body weight will be supported by the harness system.

### TMS: recording systems and electrophysiological parameters

3.9

MEPs will obtained through magnetic monophasic stimuli delivered through a high-power Magstim200 Stimulator (Magstim, Whitland, Dyfed, UK). The coil will be placed tangentially to the scalp with the handle pointing backwards and laterally, at a 45-degree angle to the sagittal plane, approximately perpendicular to the central sulcus, on the optimal site of the scalp to get the wider MEP amplitude (motor hot-spot), from the APB muscle of the most affected side. The rise time of the magnetic monophasic stimulus will be about 100 μs with a to-zero of about 800 μs. The current flowed in handle direction during the rise-time of the magnetic field, thus with a posterior-anterior direction. We preliminarily will evaluated the resting Motor rMT, defined as the smallest stimulus intensity able to evoke a peak-to-peak MEP of 50 μV in rest APB, in at least 5 of 10 tracks consecutively, and active motor threshold (aMT), defined as the minimum stimulator output that produced MEP of 100 μV more in at least 5 of 10 trials with a constant background contraction of 20% of the maximum integrated electromyography. Then, well applied an intensity of stimulation to obtain an MEP amplitude of ∼0.7 mV. SICI and ICF will be determined according to the paired-pulse method described by Kujirai and co..^[9]^ The intensity of the conditioning stimulus will be set at 80% of aMT. The intensity of the test stimulus (TS) will set to elicit peak-to-peak MEPs amplitude of 0.7 mV. Such intensities will be kept constant throughout the experiment. SICI and ICF will be assessed at an interstimulus interval of 2 and 12 ms, respectively. Mean amplitude of the conditioned MEP will be expressed as percentage of the amplitude of the unconditioned MEP and will be taken as a measure of corticospinal excitability.

Electromyographic activity will be recorded through Ag-AgCl surface electrodes applied to APB using a classic muscle belly-tendon montage. Signals will be amplified and filtered (from 32 Hz to 1 KHz) via a Digitimer D150 Amplifier (Digitimer Ltd., Welwyn Garden City, Herts, UK), and stored using a sampling frequency of 10 KHz on a personal computer for off-line analysis (Signal Software, Cambridge Electronic Design, Cambridge, UK).

### Outcome measures

3.10

Patients will be clinically evaluated by means of an accurate neurological examination by a blind to treatment physician through validated scales: EDSS, Functional Independence Measure (FIM), MAS, NRS, 10mW, 6 minute walking test (6MW), Hamilton rating scale for Depression (HRSD), and MSQOL 54. Muscular stiffness and strength will be also evaluated by means of instrumental measures furnished by the neurorobotic device itself. Moreover, cortical plasticity will be evaluated by means of TMS methodology. Finally, blood pressure and mean heart rate will be assessed.

### Participants Timeline

3.11

#### Pre-screening Visit

3.11.1

Evaluation of inclusion and exclusion criteria. Signature of informed consent.

#### Visit 1 (baseline)

3.11.2

Medical history with particular regard to antispastic drug intake. FIM, MAs, NRS, 10mW, 6MW, HRSD, and MSQOL 54. Muscular stiffness and strength will be evaluated by means of instrumental measures furnished by the neurorobotic device itself. Neurophysiological measure will be also assessed.

#### Visit 2 (at the end of rehabilitative program)

3.11.3

FIM, MAs, NRS, 10mW, 6MW, HRSD, and MSQOL 54. Muscular stiffness and strength will be evaluated by means of instrumental measures furnished by the neurorobotic device itself. Neurophysiological measure will be also assessed.

#### Visit 3 (1 month after the last robotic-rehabilitative session)

3.11.4

FIM, MAs, NRS, 10mW, 6MW, HRSD, and MSQOL 54. Muscular stiffness and strength will be evaluated by means of instrumental measures furnished by the neurorobotic device itself. Neurophysiological measure will be also assessed.

### Sample size

3.12

On the basis of the pilot samples during study, we calculated a minimal sample size of 36 participants per group in this study, given a power of >80% to detect an interaction in the 2-way repeated measures, an effect size of 0.61, 7 variables, and 4 repeated measurements. Neurophysiological measure will be also assessed.

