### Statistical analysis

3.13

The Wilcoxon signed ranks test on the T0-T1-T2 differences concerning the different clinical outcome measures (EDSS, FIM, MAs, 10mW, 6MW, HSD, MSQOL 54) will be carried out in both groups. The α-level for significance will be set at *P* < 0.05. The Bonferroni correction will be used in multiple comparisons. Data will be expressed as mean or percentage ± standard deviation. The effects of the treatment on RMT, peak-to-peak MEP amplitude, SICI, and ICF will be evaluated in separate repeated-measures analyses of variance (rmANOVA). For each dependent variable, we will compute a 2-way rmANOVA with time (4 levels: T_0_- T_1_-T_2_) and group (2 levels: group A and group B) as within-subject factors. Conditional on a significant F value, post-hoc paired-sample *t* tests were performed to explore the strength of main effects and the patterns of interaction between experimental factors. The Greenhouse-Geisser method will be used if necessary to correct for nonsphericity. All data will be given as means or percent ± standard error. We also will calculate a Fisher Z-transformation concerning the correlations between clinical and electrophysiological parameters.

This is a pilot study. The main aim is to provide evidence which could allow planning of a further confirmatory study. The simple size of 40 patients was determined on the basis of feasibility criteria. Consequently, no formal statistical hypothesis was done

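### The sample-size section claims more than 80% power with at least 36 per group, but the trial plans 20 per group on feasibility grounds, so the claimed power does not apply to it

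*Protocol article*

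**What the plan says.** Section 3.12 (Sample size) of the protocol article states: "we calculated a minimal sample size of 36 participants per group in this study, given a power of >80" per cent. The target is "to detect an interaction in the 2-way repeated measures" analysis. The inputs are "an effect size of 0.61, 7 variables, and 4 repeated measurements", and their source is given as "On the basis of the pilot samples during study", with no data shown.

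Section 3.2 (Eligibility criteria) plans 40 patients: "20 of them in treatment with Sativex (Group A) considered as responders, and 20 treated only" with other antispastics. The Abstract and section 3.4 give the same 20 and 20. Sections 3.6 and 5.5 repeat the total of 40.

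Section 3.13 (Statistical analysis) ends by calling the trial a pilot: "The simple size of 40 patients was determined on the basis of feasibility criteria". It adds that there is therefore no formal hypothesis.

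On the number of measurements, section 3.6 schedules three assessments (baseline, T1, T2), and sections 3.11.2 to 3.11.4 describe three visits. Section 3.13 gives the time factor four levels but lists only T0, T1 and T2.

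**The concern.** Two bases for the size of the same trial stand in adjacent sections. One is a calculated minimum with a power attached. The other is a feasibility number with no hypothesis. The plan follows the second, 16 patients per group below the first, and does not withdraw the first.

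Two things are at stake. A reader of section 3.12 alone could take a null interaction as coming from a trial with more than 80% power. And section 3.13 says the purpose is to inform a confirmatory study, so 36 per group may be carried forward as a planning figure although it rests on a measurement count this trial does not have and on inputs that are not fully stated.

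**Working it through.** **Inputs from the protocol article.** 36 per group, power above 80%, effect size 0.61, 7 variables, 4 repeated measurements, test of an interaction (3.12). Significance level 0.05, sidedness not stated; "The Bonferroni correction will be used in multiple comparisons", which 3.12 does not mention (3.13). Planned size 20 per group (3.2). Three assessments (3.6, 3.11).

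**Not given.** Which metric 0.61 is in, sidedness, correlation between visits, the sphericity assumption (3.13 foresees a Greenhouse-Geisser correction if needed), and what the 7 variables are. Section 3.13 lists seven clinical scales, but these go to Wilcoxon tests. The repeated-measures ANOVA is planned for four TMS measures.

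**Step 1. Shortfall against the stated minimum.** 2 × 36 = 72 needed, 2 × 20 = 40 planned: 32 fewer in total, 16 fewer per group.

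**Step 2. Can 36 per group be reproduced?** Each reading of 0.61 below uses alpha 0.05 and 80% power.

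*Standardised mean difference d, two groups* (noncentral t, df = 2n − 2, noncentrality d√(n/2)):

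| n per group | Power, two-sided | Power, one-sided |
|---|---|---|
| 20 | 46.8% | 59.9% |
| 34 | 69.8% | 80.1% |
| 36 | 72.3% | 82.1% |
| 43 | 79.8% | 87.7% |
| 44 | 80.8% | 88.4% |

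Two-sided, 44 per group are needed and 36 falls short. One-sided, 34 suffice, and 36 fits a claim of more than 80%.

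*Cohen's f for the interaction, usual convention* (noncentral F, m visits, df m − 1 and (N − 2)(m − 1), noncentrality λ = f²Nm/(1 − ρ), f² = 0.61² = 0.372). With sphericity, 3 or 4 visits and ρ from 0 to 0.7, 80% power is reached with 6 to 12 patients in total. With the lower-bound epsilon at ρ = 0 it takes 18. At N = 40, power is above 99% in all of these.

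*Cohen's f, with λ = f²N instead.* At 4 measurements, 32 in total under sphericity and 66 (33 per group) with the lower-bound epsilon. In that last case, at N = 40, λ = 0.372 × 40 = 14.9; multiplied by 1/3 this is 4.96 on 1 and 38 df, which gives about 58% power.

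*d = 0.61 taken as f = 0.305 for the interaction, usual convention.* At 4 measurements, ρ = 0 and lower-bound epsilon, 66 in total; fewer with higher correlation or with sphericity.

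Some readings come close to 36 per group and others are far from it. The document does not say which was used.

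**Step 3. Power at 20 per group if the stated minimum is taken at its word.** Find the effect that gives exactly 80% power at N = 72 and evaluate it at N = 40. For the interaction F test λ is proportional to N, so it falls by 40/72 = 0.556, and neither the metric nor ρ needs to be known.

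| Test | λ at N = 72 | λ at N = 40 | Power at N = 40 |
|---|---|---|---|
| Interaction, 3 visits, sphericity | 9.84 | 5.47 | 52.5% |
| Interaction, 4 visits, sphericity | 11.11 | 6.17 | 51.5% |
| Interaction, lower-bound epsilon | – | – | 54.1% |
| Two-group t, two-sided | – | – | 54.1% |

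A one-sided t test would give 57.7%, but the interaction F test named in 3.12 has no direction.

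**Step 4. What 20 per group buys in a simple two-sided comparison of two means.** 95% CI half-width = t(0.975; 38) × √(2/20) = 2.024 × 0.316 = 0.64 SD. Difference detectable with 80% power = 0.91 SD.

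**The case against.** The strongest defence is that the article calls the trial a pilot twice (3.1 and 3.13), and that the section directly after 3.12 says 40 was chosen on feasibility without a hypothesis. A reader of both sections is told that the trial is not powered. This limits the harm but does not remove the conflict: 3.12 states its minimum for this study, and nothing withdraws it. Condensation into an article does not explain it either, since both statements are printed.

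A reader might go further and infer that the 36 is an arithmetic error. The documents do not support that. Two-sided d = 0.61 and the usual interaction f both miss 36, but one-sided d = 0.61 needs 34 per group, and some settings of correlation, epsilon and convention come near 72 in total. The supportable statement is that 36 cannot be verified.

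A reader might also infer that the trial simply has about half the power it needs. That too is conditional. The 52–54% assumes that 72 patients give exactly 80%, whereas 3.12 says more than 80%. If 0.61 is an interaction f under the usual convention, power at 40 patients is above 99%; but then 36 per group is not a minimum, and section 3.12 still needs correcting.

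It is also fair to say that the 0.64 SD and 0.91 SD figures do not describe the planned tests, which are within-group Wilcoxon tests and repeated-measures ANOVA. They need to be labelled accordingly.

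**Conclusion.** The point holds as an internal contradiction. The protocol calculates a minimum of 36 per group for more than 80% power, plans 20 per group, and bases that number on feasibility with no hypothesis. The claimed power therefore does not apply to the planned trial by the protocol's own calculation. The measurement count in the calculation (four) also conflicts with the schedule (three), and the time factor in 3.13 repeats the error.

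The size is 16 patients per group below the stated minimum. Conditional on 72 patients giving exactly 80% power, 40 give about 52–54% for the same effect.

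Neither a miscalculated 36 nor an unconditional halving of power is established, because the metric, sidedness, correlation and sphericity assumption are not stated. Nor does the point imply that the trial must enrol more patients: feasibility can be a sufficient basis for a pilot if it is the only one given.

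**What to change.** 1. Remove the 36-per-group, more-than-80%-power statement from 3.12 as the basis for this trial, and keep feasibility (40 patients, 20 per group) as the single basis. Alternatively, recalculate with the effect-size metric, sidedness, correlation, sphericity assumption and three time points stated, and report the resulting power at 20 per group.
2. Change four measurements to three in 3.12, and four time levels to three in 3.13.
3. State what 20 per group gives, for example a 95% CI half-width of about 0.64 SD and 80% power only for a difference of about 0.91 SD, labelled as applying to a simple two-sided comparison of two group means and not to the Wilcoxon or repeated-measures tests.

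The cost is wording and, if the second option is taken, a short recalculation. No extra patients and no change of design or analysis are needed. The price is a less favourable stated figure.
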